**Figure 1 figure1:**
[figure not shown]
A sample of the mobile app interface before usability testing.

### Data Collection

Tasting samples or prepared dishes specific to the cancer prevention guidelines (eg, replace refined grains with whole grains, reduce red and processed meat consumption, consume at least 5 fruits and vegetables per day, reduce portion sizes to lower body weight, and lose even small amounts of body weight) will be distributed. Participants will complete a sensory evaluation of the appearance, taste, texture, aroma, and overall acceptability of dishes prepared during cooking demonstrations. With a Likert scale, participants will be asked to rate each dish from 1 (unattractive; flavor did not appeal to me; inappropriate texture; unappetizing aroma; unacceptable) to 5 (extremely attractive; tasted great; great texture; smelled good; extremely acceptable). A discussion of the sensory evaluation results at the end of the cooking videos will be used to show app users the acceptability of the featured dishes.

Focus group discussions and responses to key informant interviews will be digitally recorded, transcribed verbatim, manually coded, and summarized. Data will be analyzed using Qualitative Content Analysis [26]. Coding steps will include developing preliminary themes creating additional codes based on themes that arise, developing non-substantive codes, and producing detailed codes for analysis of specific topics. NVivo 10 software for computer-assisted qualitative data analysis will be used to facilitate the coding process (ie, assessing the degree of agreement/disagreement across themes and calculating interrater reliability scores) [27]. A process of double coding (eg, 2 coders will code all items) will be utilized to calculate a level of agreement between coders and to determine consistency in coders. Recurring themes will be identified, the research team will come to a consensus on coded themes, and themes will be summarized for analysis.

After themes are applied, the first iteration of mCPA will be presented in a discussion forum. The discussion forum will include all SISTAAH Talk members attending monthly meetings, which will include the mCPA participants. All data related to developing the app and the app itself will be presented to determine acceptability (intention to use). Based on comments of the participants during the discussion, a second iteration of the app will be completed and made ready for testing. The second iteration of the app will be reviewed by the technology expert, principal investigator, and support group leaders, who will decide that the app is ready for pilot testing. This process will strengthen content validity and permit user input into intervention development.

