## Methods

### Study Population

Established in 1995 as the first breast cancer support group for women of color in South Florida, the goal of SISTAAH Talk is to provide a forum for African-Americans to communicate about and make sense of their diagnosis and treatment in order to achieve improved physical and mental health outcomes. SISTAAH Talk includes women from across Miami-Dade and Broward counties, reaching an average of 20 women each month through education, outreach, and research. In 2013, SISTAAH Talk breast cancer survivors (N=240) participated in focus group discussions and completed lifestyle assessments for the National Institute of Minority Health & Health Disparities-funded pilot study, Assessing Lifestyle Modification Needs & Experiences of African American Women [13]. Four focus group discussions (n=42; mean age 45.73 years, SD 7.91, range 35-75 years) identified barriers to and intervention approaches for enhancing dietary intake and PA. Themes emerging from content analysis converged into the following categories: practical tools (goal setting, self-monitoring), talk as central, led by BCSs, support group approach, “hands-on” or interactive nutrition (cooking) and physical activity education, and community-based (not community placed) research. The findings of these focus group discussions will be combined with theories in an intervention planning process between investigators and BCSs to inform the design of mCPA.

SISTAAH Talk members (n=12), treated for >1 year for Stages I-IIIc breast cancer, 75 years of age or younger, and English speaking/writing, were identified by leaders of the support group as good role models to participate in developing mCPA. Each applicant was interviewed by the principal investigator and support group facilitator to determine comfort level in participating in focus group discussions, key informant interviews, and app content development (eg, videotaping cooking demonstrations and PA).

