Four 90-minute focus groups with 12 SISTAAH Talk members and led by investigators, will explore three factors: performance expectancy, effort expectancy, and participant-centered factors. Performance expectance is defined as the degree to which a BCS believes that using the app will help attain lifestyle goals. Effort expectancy is the degree of ease associated with use of the app. Participant-centered factors include developing an app that is respectful of and responsive to user preferences, needs, and values, and ensuring that BCSs guide the development process. Acceptability will be determined by attitudes towards technology, anxiety, self-efficacy, and behavioral intention (eg, intent to use the app). Usability will be measured based on facilitating conditions and user-friendliness.

Three key informant interviews for each participant (n=36) will be conducted to ensure that perspectives across mCPA users are captured. Participants will be charged at baseline, midway, and postdevelopment with reviewing the app to make suggestions for adaptations and refinements and determine acceptability. Key informants will be provided access to the app, as it is being developed, and asked for feedback as part of a telephone follow-up.

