### Data Analyses

mCPA acceptability, feasibility, and accessibility will be evaluated using descriptive statistics of frequency and proportion for discrete data and means and standard deviations for continuous data. All analyses will be accomplished with SAS version 9.4.

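### The forum determines other members' intention to use the app while showing them their peers' evaluations of it

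*Protocol article*

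**What the plan says.** In the protocol article, Data Collection places the forum after the qualitative analysis: "After themes are applied, the first iteration of mCPA will be presented in a discussion forum". On the audience it says: "The discussion forum will include all SISTAAH Talk members attending monthly meetings, which will include the mCPA participants". On purpose and material it says: "All data related to developing the app and the app itself will be presented to determine acceptability (intention to use". On what follows it says: "Based on comments of the participants during the discussion, a second iteration of the app will be completed and made ready for testing".

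Acceptability is also assessed elsewhere. For the focus groups, the section on app development says: "Acceptability will be determined by attitudes towards technology, anxiety, self-efficacy, and behavioral intention (eg, intent to use the app". For the key informant interviews it says: "Participants will be charged at baseline, midway, and postdevelopment with reviewing the app to make suggestions for adaptations and refinements and determine acceptability". Data Analyses then states: "mCPA acceptability, feasibility, and accessibility will be evaluated using descriptive statistics of frequency and proportion for discrete data".

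**The concern.** To say whether she would use the app, a woman has to see the app. She does not have to see what others thought of it. The plan combines the two, and gives the combined presentation as the means of determining intention to use.

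The evaluations come from women the other members know, whom the group's leaders put forward as examples to others (Study Population), and these women attend the forum. A stated intention given in that setting mixes a member's own reaction to the app with her knowledge of her peers' reaction. A favourable shift is plausible.

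An acceptable app is part of the study hypothesis (Introduction). If the forum result is read as the view of members who did not build the app, it may look better than the reaction of a woman who meets the app without that background. Shifted answers cannot be corrected in the analysis, so the remedy has to lie in how the forum is run.

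**Working it through.** The article states no figure for the forum, so there is nothing to reproduce. The check sets the relevant statements side by side.

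1. **Material and purpose (Data Collection).** Development data and app are joined in one clause, and both are shown for the purpose of determining intention to use. Followed as written, the answer is given with knowledge of both.

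2. **Content of the data.** The forum takes place after the themes have been applied, so the focus group and interview findings exist by then. The app development section describes four focus groups with the 12 participants and three interviews each (12 × 3 = 36). What they yield is the evaluation of the app by those 12 women. The sensory ratings of the dishes are also data from the development work.

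3. **Audience.** The forum is open to all members who attend the monthly meetings, and the 12 are expressly included. Other members thus see the evaluations in the presence of the women who gave them.

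4. **Response.** The only response described is comments in the discussion, and the text links these to the second iteration of the app. It names no instrument for intention to use and does not say at what moment the answer is taken.

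5. **Other acceptability sources.**

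| Source | Who answers | Outside the 12? |
|---|---|---|
| Focus groups | The 12 participants | No |
| Key informant interviews (baseline, midway, postdevelopment) | The same 12 | No |
| Discussion forum | All attending members, including the 12 | Yes |

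The forum is therefore the only described source of acceptability from women who did not help build the app.

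6. **Would excluding the 12 solve it?** No. The remaining members would still answer with knowledge of the development data. Reporting the 12 separately is useful, but it does not replace the change in order.

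**The case against.** The strongest reply is that the forum is formative. Data Collection says it serves content validity and user input. Open discussion of findings with the community is the chosen participatory method (Introduction; Table 1). Readiness for pilot testing is decided by the technology expert, the principal investigator and the support group leaders after the second iteration, and no threshold on a forum proportion is stated. All of this stands and limits the weight of the point. It does not remove it, because the same section also gives the forum a measuring purpose, and both purposes can be met in one meeting.

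Several stronger readings are tempting, but the article does not support them:

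- **The data are shown before the app.** The clause names both without an order. What the text supports is that the two are presented together for the purpose of determining intention.
- **Acceptability is taken from open comments, so silent members leave no answer.** The comments are linked to the revision. How intention is recorded is not stated, and a condensed article may leave that to documents not shown.
- **The forum supplies the proportion in Data Analyses.** That section speaks of acceptability in general and does not say which source feeds which statistic. The article elsewhere describes acceptability by frequency and duration of usage.
- **The dish ratings distort the answer.** In part they belong to the app, since a discussion of them at the end of the cooking videos is meant to be seen by users. An ordinary user would meet them too.
- **The effect can be sized.** A reader might subtract the 12 from the figure in Study Population, "reaching an average of 20 women each month through education, outreach, and research", and get 20 − 12 = 8 other members, so that each answer moves a proportion by 1/8, or 12.5 percentage points. But that figure describes monthly reach, not forum attendance, and the subtraction assumes that all 12 attend. The result shows only how coarse a proportion in eight women is. It would be the same with private ratings and says nothing about bias.

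**Conclusion.** The point holds in a limited form. As described, the forum obtains intention to use from members outside the 12 with knowledge of their peers' evaluations and in those peers' company, and no other described source covers such members. This rests on two readings: that presenting material in order to determine intention means the answer is given with knowledge of that material, and that the full development data include the focus group and interview findings. Both are the natural reading, but neither the sequence nor the instrument is spelled out.

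The size of any bias cannot be quantified from the article, and no figure should be attached to it. No effect estimate is at stake. What is affected is how the forum's acceptability result can be interpreted. This is a worthwhile, inexpensive improvement, not an error that undermines the study.

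**What to change.** Set the order of the forum in Data Collection:

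1. Show the app, including any dish-rating content built into it.
2. Collect a one-item written intention-to-use rating from each attendee individually, marked as mCPA participant or other member.
3. Only then present the focus group and interview data, and hold the discussion that guides the second iteration.

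Add to Data Analyses that the written ratings are summarised as the forum's acceptability result, with the 12 mCPA participants shown separately from other members, and that the discussion is used only for revisions.

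The cost is a one-item card and a few minutes at a meeting already planned, and possibly a less favourable figure. The participatory discussion is kept in full.

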### Data Analyses

mCPA acceptability, feasibility, and accessibility will be evaluated using descriptive statistics of frequency and proportion for discrete data and means and standard deviations for continuous data. All analyses will be accomplished with SAS version 9.4.

## Results

It is anticipated that development of an acceptable (frequency and duration of usage), feasible (structure, ease of use, features), and accessible mobile app will be available for intervention testing in early 2017.

## Discussion

### Principal Considerations

We expect the mobile-enabled, Web-based app (mCPA), which is theory-based and culturally tailored, to lead to multicenter, randomized controlled trials of its effectiveness in promoting healthy dietary intake and physical activity among African-American breast cancer survivors. An effective, research-tested mobile intervention to assist survivors in adopting and maintaining healthy behaviors would fill a gap in the current evidence based on culturally appropriate, low-cost interventions that can help African-American women maximize their health and quality of life following a breast cancer diagnosis. The availability of effective mHealth interventions for survivors would allow for future dissemination and implementation in order to reach large numbers of women at a relatively low cost.

Apps for patient self-management, such as the mCPA, empower women to take control of their own health and come to terms with what is often a frightening and anxiety-provoking diagnosis. The use of new technologies, apps, and social media for patient self-management of their illness and to reduce the risk of recurrence can be contrasted with computer-based programs that allow for providers to communicate with their patients as part of breast cancer treatment and survivorship care. The latter are closely tied to clinical care and may not be accessible or affordable to all groups of breast cancer survivors.

### Conclusions

Depending on the availability of research funding, mCPA testing, which will be initiated in Miami, will be extended to Chicago, Houston, Philadelphia, and Los Angeles. Results from the current study may lead to refinements, such as developing culturally tailored components of the app for ethnic subgroups of US blacks (eg, English-speaking Haitian-, and Caribbean-born blacks).

## Appendix

Multimedia Appendix 1 Topic and interview guides.

## Abbreviations

AA: African-American
AICR: American Institute on Cancer Research
BCSs: breast cancer survivors
BMI: body mass index
DHHL: Down Home Healthy Living
EPICS: Educational Program to Increase Colorectal Cancer Screening
HBM: Health Belief Model
IRB: Institutional Review Board
mCPA: mobile Cancer Prevention App
PA: physical activity
SISTAAH: Survivors Involving Supporters to Take Action in Advancing Health
SMART: specific, measurable, actionable, realistic, time-sensitive
TPB: Theory of Planned Behavior
